### Data management and quality control

The investigators in the research team were required to attend a training workshop before recruitment. Each one received a copy of the study protocol and they were asked to adhere to the protocol during the study period. The investigators responsible for collecting data received training on how to perform CVAS and quality of life assessments. The lung function and blood tests will be done by medical professionals.

Data will be collected and recorded on case report forms. All data will be entered into a predesigned password-protected database by personnel blinded to group allocation. Data entry will be performed continually throughout the trial using the double-entry method, with any corrections or changes of data written in the case report forms documented and dated. Data quality will be checked regularly by a qualified specially assigned person. The Guangdong International Clinical Research Center of Chinese Medicine (Guangzhou, China), which is independent of the sponsor and does not have any competing interests, will be responsible for monitoring the data. The Department of Science Research of GPHCM, which is independent of the sponsor and investigators, will perform data audits in the middle of the trial.

### Statistical analysis

The data analysis will be carried out by an independent statistician using PASW Statistic 18.0 (IBM SPSS Inc., Armonk, New York, USA). Continuous data will be presented as means and standard deviations, or 95% confidence intervals. Dichotomous data, such as relapse of symptoms, will be presented as risk ratios and 95% confidence intervals. Two-tailed *P* values < 0.05 are considered to be statistically significant.

Baseline characteristics will be described using standard statistical analysis methods. The categorical variables will be analyzed via chi-squared tests or Fisher’s exact analyses, while continuous variables will be analyzed using *t*-tests. The main analyses include an intention-to-treat analysis and a per-protocol subject analysis for the primary outcomes. The last observation carried forward method will be used in the intention-to-treat analysis for missing data imputation. CVAS will be calculated as monthly averages, which will be compared with the average for the 2-week run-in period. Quality of life, lung function, and blood tests will be compared with the measurements from the end of the run-in period. Differences in changes from baseline to each time point between the two groups will be compared using analyses of variance. Paired *t*-tests will be used to compare data from before and after treatment in the same group. In the analysis of factors affecting the outcome changes, mixed-effects linear or logistic regression models will be performed, adjusting for baseline characteristics and other variables. Descriptive analyses and chi-squared tests or Fisher’s exact tests will be used for the safety data analysis. Any causality between AEs and the interventions will be taken into account.

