## Background

Cough variant asthma (CVA) is the most common cause of chronic cough [1–3]. According to a Chinese epidemiological survey, CVA accounts for 1/3 of cases of chronic cough [4]. In Japan, this proportion reaches 42.2% [5]. Long-term and constant coughing seriously affects the quality of life of patients with CVA. Such patients tend to be more depressed and anxious than classic asthma outpatients, on average [6]. Currently, maintenance therapy with a combination of inhaled corticosteroid and long-acting β2-agonist (ICS/LABA) is recommended for the treatment of CVA [7–9]. After discontinuing the anti-inflammatory treatment, cough symptom scores may increase, and lung function and eosinophilic airway inflammation may become aggravated and return to their baseline levels. The cumulative relapse rate of symptoms is as high as 67% after discontinuing treatment for 6 months [7].

Chinese herbal medicine (CHM) is widely used for CVA in China. It is reported that CHM plus ICS/LABA is better at reducing cough symptom scores, improving lung function, and improving quality of life compared with ICS/LABA alone [10–12]. Studies have also suggested that CHM plus ICS/LABA could further reduce levels of serum inflammatory factors, such as IL-10, IL-17, and IL-4/IFN-γ, compared to treatment with ICS/LABA alone [13, 14]. Furthermore, CHM plus ICS/LABA is better at reducing levels of airway neurotransmitters in the sputum than ICS/LABA alone [11]. Another study showed that compared to ICS/LABA alone, CHM plus ICS/LABA was superior at inhibiting airway remodeling in patients with CVA [15]. Although many clinical studies have proven that CHM plus ICS/LABA is superior to ICS/LABA alone for the treatment of CVA, the methodological quality of these studies was low because of the absence of sample size calculations, lack of definite random methods, unclear use of blinding methods, and so on. Furthermore, in only one study did participants undergo a follow-up period after stopping treatment [12]. How do cough symptoms, lung function, and airway inflammation change after stopping treatment with CHM plus ICS/LABA? Do these outcomes show a greater improvement after treatment with CHM plus ICS/LABA compared to after treatment with ICS/LABA alone? These questions remain to be determined.

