Based on a review of the literature and clinical observation, we predicted that our prescription plus ICS/LABA may be better at relieving coughing, improving lung function, and alleviating airway inflammation compared to ICS/LABA alone, even after the discontinuation of treatment. An observational study with a small sample size of 20 was carried out at a respiratory outpatient department. The control group was treated with ICS/LABA, while the experimental group was treated with ICS/LABA plus CHM. During the 12-week treatment period, the cough visual analog scales (CVAS) decreased from 5.13 ± 1.42 (mean ± standard deviation) to 1.21 ± 0.93 in the control group and from 5.11 ± 1.10 to 0.8 ± 0.69 in the experimental group. However, at the end of the 24-week follow-up phase, the CVAS increased to 4.50 ± 2.72 in the control group and 2.36 ± 2.54 in the experimental group. In addition, the cumulative percentages of patients whose symptoms worsened were 60% in the control group and 20% in the experimental group at the end of the follow-up period. We observed that ICS/LABA plus CHM was better for the treatment of CVA than ICS/LABA alone, not only during the 12-week treatment phase but also during the 24-week follow-up phase. Therefore, we have designed a randomized controlled trial to evaluate the long-term efficacy and safety of CHM plus ICS/LABA for the treatment of CVA.

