### Trial procedure

The entire trial consists of a screening assessment, a 2-week run-in period (weeks −2 and −1), a 12-week treatment period (weeks 1 to 12), and a 24-week follow-up period (weeks 13 to 36) (Fig. 2).

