### Outcome measures

#### Primary outcome

The primary outcome is CVAS change from baseline to the end of the follow-up phase (week 36). CVAS is used to assess the participants’ perceptions of the severity of their cough. Participants will be asked to draw a vertical line intersecting a 10-cm horizontal line to indicate the severity of their cough: zero is no cough while 10 cm is the worst cough imaginable [30].

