### Termination and withdrawal

The trial will be terminated for any participant who develops one or more of the following conditions during the trial: (1) CVA develops into typical asthma, (2) intolerable side effects, or (3) serious acute or chronic organic disease. Any participant can withdraw from the trial for any reason at any time without prejudicing current or future treatments. The investigators will try to contact any withdrawn or terminated participants to complete the final assessment. Reasons for withdrawal or termination and the last medication time will be recorded. All withdrawn and terminated cases will be reported and analyzed.

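### LOCF for a week-36 cough score ignores the rebound the protocol itself expects after week 12; losses soon after treatment stops distort the group difference, towards no effect if loss is equal in the two arms

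*Protocol article*

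**What the plan says.** All references are to the protocol article.

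- **Endpoint.** The Primary outcome section takes CVAS change from baseline to week 36. Trial procedure sets 12 weeks of treatment followed by 24 weeks of follow-up, so the endpoint lies 24 weeks after treatment ends.
- **Missing data.** Statistical analysis: "The last observation carried forward method will be used in the intention-to-treat analysis for missing data imputation". No other method is named for the intention-to-treat comparison. A per-protocol analysis is also planned. The mixed-effects models mentioned there are for factors that affect outcome changes, not for the primary comparison.
- **What is carried forward.** CVAS is recorded daily to week 36 and analysed as monthly averages against the run-in average.
- **Expected course on treatment.** In the observational study (Background), CVAS moved "from 5.13 ± 1.42 (mean ± standard deviation) to 1.21 ± 0.93 in the control group" and "from 5.11 ± 1.10 to 0.8 ± 0.69 in the experimental group" over 12 weeks.
- **Expected course off treatment.** By the end of follow-up the means were 4.50 (SD 2.72) in controls and 2.36 (SD 2.54) with CHM. From the literature, Background adds: "The cumulative relapse rate of symptoms is as high as 67% after discontinuing treatment for 6 months".
- **Losses.** Sample size estimation allows 20% for loss and non-compliance together. Termination and withdrawal says that investigators will attempt a final assessment of those who leave.

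**The concern.** LOCF assumes that a patient's score stays where it was when last seen. This trial is built on the opposite expectation: scores are lowest at the end of treatment and climb once it stops. A low score from around week 12, carried to week 36, stands in for the off-treatment course that the trial sets out to measure.

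The expected rise also differs between arms, so the error does not cancel in the contrast. Equal and purely random loss would still distort it, and unequal loss could push it either way. At stake is the primary estimate and, under unequal loss, the type I error. Single imputation also treats filled-in values as observed, so the standard error does not reflect the missing information.

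**Working it through.** **Inputs.** Week-12 means (SD): control 1.21 (0.93), CHM 0.80 (0.69). Week-36 means (SD): control 4.50 (2.72), CHM 2.36 (2.54). All are from Background. Assumed, because the article does not give them: loss rates by arm, and loss just after week 12 unless stated. I work with score levels; baselines of 5.13 and 5.11 change the difference by only 0.02 (2.12 for change against 2.14 for level).

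**1. The plan's own figure.** The SD is not stated. The pooled week-36 SD is √((2.72² + 2.54²)/2) = 2.63. Then n = 2 × (1.960 + 1.282)² × 2.63² / 2.5² ≈ 23.3, so 24 per group, and 24/0.8 = 30. The stated sample size reproduces and is not at fault.

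**2. Error per lost patient.** Control: 4.50 − 1.21 = 3.29 cm too good. CHM: 2.36 − 0.80 = 1.56 cm too good.

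**3. LOCF difference.** With loss proportion d, an arm's mean is (1 − d) × week-36 mean + d × carried mean.

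| Loss, control / CHM | Control mean | CHM mean | Difference |
|---|---|---|---|
| none | 4.50 | 2.36 | 2.14 |
| 20% / 20% | 0.8 × 4.50 + 0.2 × 1.21 = 3.84 | 0.8 × 2.36 + 0.2 × 0.80 = 2.05 | 1.79 |
| 10% / 10% | 4.17 | 2.20 | 1.97 |
| 30% / 10% | 3.51 | 2.20 | 1.31 |
| 10% / 30% | 4.17 | 1.89 | 2.28 |
| 20% / 20%, lost midway through the rebound | 4.17 | 2.20 | 1.97 |

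In the last row the carried means are the midpoints, (1.21 + 4.50)/2 = 2.855 and (0.80 + 2.36)/2 = 1.58.

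**4. Direction.** Bias in the difference = d(CHM) × 1.56 − d(control) × 3.29. It is positive, favouring CHM, only when d(CHM)/d(control) exceeds 3.29/1.56 = 2.11. With equal loss it is always negative.

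**5. Power** (two-sided 0.05, noncentral t, true difference 2.14).

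- No missing data, 30 per arm: noncentrality 2.14/2.63 × √15 = 3.15; power 87%.
- 24 completers per arm, lost at random: 2.14/2.63 × √12 = 2.82; power 79%.
- LOCF with 20% / 20%: mixture SDs 2.80 and 2.38, pooled 2.60; 1.794/2.595 × √15 = 2.68; power 75%.
- LOCF with 30% / 10%: pooled SD 2.63; 1.309/2.625 × √15 = 1.93; power 48%.

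**6. No true week-36 difference.** Let both arms follow the control course, with 10% control and 30% CHM loss at week 12. The expected false benefit is (0.30 − 0.10) × 3.29 = 0.66 cm. In simulation with 30 per arm and scores limited to 0–10, it is 0.65 to 0.68 cm. Type I error is about 13% when the number lost per arm is fixed and scores outside the scale are set to its ends. It reaches about 19% when loss is random and the score distribution is truncated. At 10% / 20% it is about 5% to 8%. At 20% / 20% it does not exceed 5%.

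**The case against.** A reader might infer that everyone lost during follow-up is scored as a lasting success, or that LOCF tilts the trial towards CHM. The documents support neither.

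- **Timing.** Diaries run daily to week 36, so only losses at or near week 12 carry the lowest scores. Later losses carry a partly rebounded average, and losses early in treatment carry something near baseline.
- **Relapse-driven dropout.** A patient who leaves because of worsening, including one terminated because CVA has become typical asthma, may already have recorded it. LOCF would then carry a poor score.
- **Direction.** Equal loss works against CHM. The observational study had more worsening in controls (60% against 20%), so nothing in the document points to a large excess of CHM loss. The 10% / 30% case is an illustrative extreme.
- **Power.** The fair comparator at 20% loss is about 79% from completers, not 87% with nothing missing. The loss due to LOCF itself is then about 4 points.
- **Rate.** The 20% allowance includes non-compliance, and non-compliant patients may still return diaries. True missingness could be lower.
- **Mitigation.** A final assessment will be attempted, a per-protocol analysis is planned, and an analysis plan not shown may add sensitivity analyses.

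These points limit the size and scope, and I accept them. They do not rescue the choice. LOCF is what the article states for the main analysis. An attempted final visit is neither guaranteed nor the diary average that is analysed. A per-protocol analysis does not deal with missing follow-up. A bias whose sign turns on unknown dropout is a poor thing to fix in advance.

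**Conclusion.** The point holds in a limited form. On the protocol's own figures, LOCF is a badly chosen primary method for an endpoint 24 weeks off treatment, because the rebound it ignores is large and differs by arm.

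- With equal loss near week 12, the result is attenuation: at 20% per arm the difference is about 16% too small (0.35/2.14), and LOCF has less power than dropping the lost patients. For loss midway through the rebound the attenuation is about 8% (0.17/2.14).
- With unequal loss near week 12, the estimate runs from 1.31 (30% / 10%) to 2.28 (10% / 30%), against 2.14.
- If the arms do not truly differ at week 36 and share the same course, any excess CHM loss soon after week 12 produces a false benefit.

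A general claim of bias in favour of CHM is not supported. All sizes rest on means from 20 patients and on assumed loss rates and timing. They show what LOCF can do here and do not predict what it did.

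**What to change.** Replace LOCF as the primary intention-to-treat method. Fit a likelihood-based mixed model for repeated measures to the nine 4-weekly CVAS averages (36/4 = 9) in all randomised patients, with arm, period, arm-by-period and run-in mean CVAS. Name the contrast at weeks 33–36 as the primary test.

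State the covariance structure in advance. An unstructured matrix over nine periods has 9 × 10/2 = 45 parameters, which is heavy for 60 patients, so a more economical structure is needed, with a small-sample degrees-of-freedom correction.

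Add a sensitivity analysis by multiple imputation, return-to-baseline or delta-adjusted, for patients lost after week 12. Keep LOCF at most as a further sensitivity analysis. Record the change before unblinding.

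The cost is a change of wording and a little programming, with no extra patients or visits. The small downside is reliance on missing at random, which the sensitivity analysis probes, and on the chosen covariance structure.

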**Fig. 2 Fig2:**
[figure not shown]
Trial flow chart. CHM Chinese herbal medicine, SFC salmeterol/fluticasone propionate combination

Potential participants will be invited to an initial assessment (first visit) consisting of screening for inclusion and exclusion criteria. If eligible, participants will be asked for informed consent and will undergo assessments of CVAS and quality of life, as well as a full blood count, blood tests on kidney and liver function, an electrocardiogram, and a chest radiograph examination. Then they will commence a 2-week run-in period. During this period, the participants’ use of asthma-related medication and CHM will be restricted. Participants will be provided with a salbutamol inhaler (Ventolin 5 mg/ml, GlaxoSmithKline, UK), to be used as required during this period to ease coughing until the treatment period begins. In the 2-week run-in period, the participants will be required to record the severity of their cough each day using the CVAS. After the run-in period, participants will undergo another set of baseline assessments (second visit), including assessments of quality of life, lung function, and blood tests.

After the baseline assessments, participants will be randomly allocated to receive 12 weeks of CHM plus SFC or placebo plus SFC. CVAS will be self-reported by the participants and recorded daily in a diary during the treatment period. Face-to-face assessments with blinded assessors will be scheduled at weeks 4 (third visit), 8 (fourth visit), and 12 (fifth visit). These will collect additional data, including lung function assessments and blood tests, as well as evaluations of quality of life, safety, and drug usage. Participants will be interviewed by telephone at weeks 2, 6, and 10 to determine adherence to the medication regulations and to report adverse events (AEs). The frequency of visits and phone calls can be increased if necessary.

During the 24-week follow-up phase, participants will continue to record CVAS daily in their diaries and document their utilization of health resources (including drug therapy use). They will attend follow-up assessments at weeks 24 and 36 (sixth and seventh visits). At each visit, quality of life, lung function, AEs, and drug usage will be assessed and participants will undergo blood tests.

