### Sample size estimation

The sample size calculation for the primary outcome needs to be statistically and clinically significant. Based on previous literature [7] and our observational study, a sample size of 24 participants in each group can achieve 90% power to dismiss from a two-sided type I error of 0.05 to detect a superiority margin difference of 2.5 in this trial with two-tailed *P* values < 0.05 indicating significance. The total sample size was adjusted to 30 participants in each group to allow for 20% loss to follow-up and non-compliance.

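### The week-36 change in CVAS is compared without the run-in CVAS as a covariate: a valid test, but one that can lose precision an ANCOVA would keep

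*Protocol article*

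**What the plan says.** All references are to the protocol article.

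- **Primary outcome:** "The primary outcome is CVAS change from baseline to the end of the follow-up phase (week 36").
- **Baseline:** the Trial procedure section states that, during the run-in, "the participants will be required to record the severity of their cough each day using the CVAS". The Statistical analysis section then makes the mean of those readings the reference: "CVAS will be calculated as monthly averages, which will be compared with the average for the 2-week run-in period".
- **Between-group test:** "Differences in changes from baseline to each time point between the two groups will be compared using analyses of variance". No covariate is attached to this comparison.
- **Where adjustment appears:** "In the analysis of factors affecting the outcome changes, mixed-effects linear or logistic regression models will be performed, adjusting for baseline characteristics and other variables". This is a separate analysis with a different purpose, and its covariates are left open.
- **Sample size estimation:** "a sample size of 24 participants in each group can achieve 90% power to dismiss from a two-sided type I error of 0.05" and "to detect a superiority margin difference of 2.5 in this trial". No planning SD is given.

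**The concern.** Subtracting baseline and comparing the differences is the same as regressing the final value on treatment with the baseline coefficient set to exactly 1. That value is optimal only if the true slope of week-36 CVAS on run-in CVAS happens to be 1. Here it may well not be. Week 36 falls 24 weeks after treatment stops, and in the pilot (Background) the SD rose from 0.93 and 0.69 at week 12 to 2.72 and 2.54 at the end of follow-up, about twice the baseline SDs of 1.42 and 1.10. If run-in cough predicts week-36 cough only weakly, subtracting it adds noise. If it predicts strongly, a slope of 1 removes too little.

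At stake is the precision of the primary estimate in a trial of 60 patients. Also at stake is how well the estimate allows for a chance difference in baseline CVAS between arms.

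**Working it through.** **Inputs.** Pilot SDs from the Background section: baseline 1.42 (control) and 1.10 (experimental). At the end of follow-up "the CVAS increased to 4.50 ± 2.72 in the control group and 2.36 ± 2.54 in the experimental group". Difference 2.5, two-sided 0.05, 90% power and 24 per arm come from Sample size estimation. Equal weights are assumed in pooling, because the pilot's arm sizes are not stated. The baseline-to-week-36 correlation ρ is not in the documents, so a range is shown.

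**Pooled SDs**
- Baseline: √((1.42² + 1.10²)/2) = √1.613 = 1.270
- Week 36: √((2.72² + 2.54²)/2) = √6.925 = 2.632

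**The plan's own figure.** n = 2(1.960 + 1.282)² × 6.925 / 2.5² = 23.3, so 24 per arm, and 24/0.80 = 30. The stated numbers are reproduced if the planning SD was the SD of week-36 values. That is an inference. By the noncentral t, power at 24 per arm is then 89.6%.

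**Variances under the two analyses**
- Change score: 6.925 + 1.613 − 2ρ(1.270)(2.632) = 8.538 − 6.685ρ
- ANCOVA: 6.925(1 − ρ²)
- Excess of the first over the second: (1.270 − 2.632ρ)². It is never negative, and is zero at ρ = 1.270/2.632 = 0.48.

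**Price of estimating the slope.** ANCOVA uses one more degree of freedom, and the variance of its treatment estimate is inflated by about 1 + 1/(2n − 4). At 24 per arm that is 1 + 1/44 = 1.023.

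**Results at 24 per arm, difference 2.5 (noncentral t).** The two ANCOVA columns ignore and include that price.

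| ρ | SD change | SD ANCOVA | Variance ratio | Slope (ρ × 2.632/1.270) | Power, change | Power, ANCOVA, price ignored | Power, ANCOVA, price included |
|---|---|---|---|---|---|---|---|
| 0 | 2.92 | 2.63 | 1.23 | 0.00 | 82.7% | 89.6% | 89.0% |
| 0.2 | 2.68 | 2.58 | 1.08 | 0.41 | 88.5% | 90.8% | 90.1% |
| 0.3 | 2.56 | 2.51 | 1.04 | 0.62 | 91.3% | 92.2% | 91.6% |
| 0.4 | 2.42 | 2.41 | 1.01 | 0.83 | 93.8% | 94.0% | 93.5% |
| 0.5 | 2.28 | 2.28 | 1.00 | 1.04 | 96.1% | 96.1% | 95.7% |
| 0.6 | 2.13 | 2.11 | 1.02 | 1.24 | 97.9% | 98.1% | 97.8% |
| 0.7 | 1.96 | 1.88 | 1.09 | 1.45 | 99.1% | 99.5% | 99.4% |
| 0.8 | 1.79 | 1.58 | 1.28 | 1.66 | 99.7% | >99.9% | >99.9% |

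**Against the inferred planning SD.** The change-score SD exceeds 2.632 when 1.613 > 6.685ρ, that is, when ρ < 0.24. The ANCOVA residual SD, 2.632√(1 − ρ²), cannot exceed it.

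**Baseline imbalance.** The 95% range of a chance difference in mean baseline CVAS is ±1.96 × 1.270 × √(2/30) = ±0.64 cm at 30 per arm, and ±0.72 cm at 24. Each centimetre of imbalance is over-corrected by 1 − 0.41 = 0.59 cm at ρ = 0.2, and under-corrected by 1.45 − 1 = 0.45 cm at ρ = 0.7.

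**The case against.** The strongest defence is that nothing here is an error. An analysis of variance of change matches an outcome defined as change, and under randomisation it is unbiased. This stands, and it makes the point one of efficiency. A reader might infer that the primary test is biased or invalid; the documents do not support that.

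A reader might also infer that chance baseline imbalance goes uncorrected. It does not: subtracting the run-in mean corrects it, though with a fixed slope that may be too large or too small.

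A third inference would be that the trial is underpowered or its sample size wrong. That would need the planning SD, which is not stated. The sample size section cites earlier literature as well as the pilot, so 2.63 is a reconstruction. It would also need a low ρ, and the documents give none.

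The gain is uncertain too. The SDs come from 20 patients in an observational study. The article does not say whether those values were single readings or averages, whereas the trial uses a 2-week mean and monthly means. The seven-point power difference belongs to ρ = 0. From ρ = 0.2 upwards the difference is about two points or less, and between about 0.35 and 0.6 the planned test is as good or marginally better. All of this stands as a limit on size.

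Two arguments carry less weight. The covariate might be thought a detail left to an unseen analysis plan, but the article itself names the test and places baseline adjustment elsewhere. If the full plan already adjusts the primary comparison, a clarifying sentence is enough. The planned mixed-effects models do adjust for baseline, but they are described as an analysis of factors and not as the treatment comparison.

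**Conclusion.** The point holds as an efficiency recommendation. The planned comparison is valid and unbiased, but by fixing the baseline slope at 1 it may lose precision and mis-correct chance imbalance.

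On the pilot SDs, its excess variance over ANCOVA ranges from nil near ρ = 0.48 to 23% at ρ = 0 and 28% at ρ = 0.8. The loss that could matter for power is at low ρ, up to about six or seven points at 24 per arm. At high ρ both analyses exceed 99% power, and the benefit is a narrower confidence interval. In the middle range ANCOVA gives up less than half a point, so the trade favours adjusting when ρ is unknown.

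This rests on the pilot SDs carrying over, a common SD and correlation in both arms, and the stated difference of 2.5. The link to the sample size holds only if 2.63 was the planning SD.

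**What to change.** Name the primary between-group comparison as an ANCOVA of the monthly mean CVAS ending at week 36, with treatment and the 2-week run-in mean CVAS as covariate. Report the adjusted mean difference with its 95% confidence interval. The change score can stay as the response if preferred: with baseline in the model, the treatment estimate is identical, so the stated primary outcome need not change. Adjust quality of life, lung function and blood markers in the same way for their own end-of-run-in values.

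**Cost:** one degree of freedom, about 2% variance inflation at this sample size, and no new data. The change needs a documented, dated amendment before unblinding. The article expected the last follow-up in mid-2018 and was published in January 2019, so the amendment should record that allocation was still concealed. The Randomization section keeps the codes confidential until the analysis is complete. If unblinding has already happened, report the ANCOVA as a supportive analysis and label it as such.
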